CFA will be used to cross-validate the plausible unidimensional structure of the PERSONAE scale derived from the MSA, theoretically containing 10-15 items, using Mplus 8.1 (Muthén and Muthén, 2017). An unrestricted and unspecified model will be used with a maximum likelihood robust estimation of parameters. A confirmatory factor analysis with covariates will be used to estimate measurement invariance between subgroups if linear relationships between participant characteristics and the scale’s total score are detected [27]. Modification indices will be explored to identify items causing a violation of invariance. Items causing invariance will be evaluated for possible deletion from the final scale. The adequacy of confirmatory factor analyses in explaining sample statistics will be assessed using various fit indices, such as chi-square, chi-square/degree of freedom, comparative fit index, Tucker-Lewis index, and root mean square error of approximation [28]. Invariance testing based on different levels of CCI and other potential confounders will be considered if needed and is feasible to ensure that the scale functions equivalently across groups with varying levels of comorbidity and demographics.

Missing data will be managed using an available-case approach for missingness lower than 5% or regression imputations for missingness equal to or higher than 5%, assuming missing at random. The significance level for all analyses will be set at 5%. The software used for the analysis will include Mplus (version 8.1, Muthén and Muthén), IBM SPSS Statistics for Microsoft Windows version 27, and R (version 4.2.1, R Foundation for Statistical Computing).

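### The only model named for measurement invariance, a CFA with covariates, assumes equal loadings across subgroups, so unequal loadings are not tested and show at most as an apparent intercept shift

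*Protocol article*

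**What the plan says.** The invariance plan is in one paragraph of the protocol article, Methods, Data Analysis.

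- **Model and purpose:** "A confirmatory factor analysis with covariates will be used to estimate measurement invariance between subgroups".
- **When it runs:** "if linear relationships between participant characteristics and the scale’s total score are detected".
- **How items are located:** "Modification indices will be explored to identify items causing a violation of invariance". The items found are then considered for deletion. The text does not say whether the indices concern loadings or intercepts.
- **Further testing:** "Invariance testing based on different levels of CCI and other potential confounders will be considered if needed and is feasible", with the aim "to ensure that the scale functions equivalently across groups with varying levels of comorbidity and demographics". No model is named for this step.
- **Setting:** a one-factor scale "theoretically containing 10-15 items", fitted by "maximum likelihood robust estimation of parameters".

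The article mentions no multigroup CFA, no test of equal loadings and no factor-by-covariate interaction. The Sample Size section leaves the second-round sample size to later Monte Carlo simulation.

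**The concern.** Measurement invariance between subgroups requires that each item relates to preparedness with the same strength (equal loadings) and from the same starting level (equal intercepts). The named model addresses the second requirement and takes the first as given. The article therefore assigns the model a question of which it can answer only part.

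An item may track preparedness closely in, say, better-educated patients and only loosely in others. The same total score then does not mean the same preparedness in the two groups. The Results section expects clinicians to use the scale to identify patients who may benefit from self-testing, so comparability of the score across patient groups matters for its intended use.

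**Working it through.** **Step 1. What the model can represent.** A one-factor CFA with covariate x is

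y = ν + Λη + Bx + e, with η = γx + ζ.

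One loading vector Λ serves every value of x. A subgroup difference can enter only through γ (latent mean) or B (direct effect, which is an item intercept shift). No parameter stands for a subgroup difference in Λ, so a modification index for a direct effect cannot identify one as such. This is algebra and depends on no assumed number.

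**Step 2. Inputs for the size.** The article gives no figure for this test, so there is none to reproduce.

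- From the article: 10-15 items (10 used), 5% level, maximum likelihood (the plain form was used).
- Assumed: N = 500 (300 as sensitivity), two equal groups, continuous items, loading 0.70, residual variance 0.51, one item with loading 0.35 or 0.50 in the second group, 400 replicates per setting.

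**Step 3. Item lines crossing at or near the mean.** The direct-effect test on the altered item (1 df) stands in for its modification index. The comparator is a 1-df test of that item's loading in a two-group CFA.

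| N | Loadings | Latent mean difference (SD) | Direct-effect test rejects | Two-group loading test rejects |
|---|---|---|---|---|
| 500 | 0.70 / 0.70 | 0 | 5.5% | 5.2% |
| 500 | 0.70 / 0.35 | 0 | 3.5% | 99.5% |
| 500 | 0.70 / 0.35 | 0.3 | 10.2% | 100% |
| 500 | 0.70 / 0.35 | 0.5 | 23.7% | 100% |
| 500 | 0.70 / 0.50 | 0 | 4.0% | 80.5% |
| 300 | 0.70 / 0.35 | 0 | 4.0% | 97.3% |

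Overall fit gives no warning. In the second row the covariate model's chi-square rejects in 8.7% and mean RMSEA is 0.009, the same RMSEA as with equal loadings.

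**Step 4. Why a mean difference leaks into the direct effect.** The pooled loading is near (0.70 + 0.35)/2 = 0.525. With a latent mean difference of 0.5, the model expects an item mean difference of 0.525 × 0.5 = 0.2625, and the true one is 0.35 × 0.5 = 0.175. The gap of 0.0875 is read as an intercept shift. At a difference of 0.3 the gap is (0.525 − 0.35) × 0.3 = 0.0525. A rough standard error is √(4 × (0.51 + 0.175²)/500) = √(4 × 0.5406/500) = 0.066. So z = 0.0875/0.066 = 1.33 and 0.0525/0.066 = 0.80, giving power of about 26% and 13%. These agree with the simulated 23.7% and 10.2%.

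**Step 5. Item lines crossing 1 SD below the mean.** The second group's line then sits lower at the mean by (0.70 − 0.35) × 1 = 0.35, or by 0.20 for 0.70 v 0.50. A separate simulation used 12 five-point items, two equal groups, 300 replicates and mean differences of 0-0.5 SD. The direct-effect test rejected as follows:

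- 0.70 v 0.35: 94-98% (N = 300) and 99-100% (N = 500).
- 0.70 v 0.50: 53-66% (N = 300) and 74-85% (N = 500).

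Here the item is usually caught, because its mean has moved. It is recorded as intercept bias, and the loading difference remains untested.

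**Step 6. What the model does well.** A true intercept shift of 0.4 with equal loadings is detected in 100% of samples at N = 500.

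**The case against.** The strongest reply has five parts.

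1. **The trigger.** The covariate model runs only where a characteristic relates to the total score. With equal latent means and a crossing at the mean, total scores would hardly differ, so the test would rarely be run. The 4% figure is thus the least favourable case, and 10-24% is more typical of triggered cases with a crossing near the mean. This stands, and the range is given for that reason. It also shows a weakness in the trigger, since loadings can differ with no total-score association.
2. **Detection off the mean.** When the lines cross well away from the mean, the item is often flagged and considered for deletion whatever its label. This stands too. A reader might infer that the model cannot detect unequal loadings at all, or that power always falls to the significance level. Neither holds in general.
3. **The aim of equivalent functioning.** A reader might infer that the article rests "to ensure that the scale functions equivalently across groups with varying levels of comorbidity and demographics" on the covariate model. It does not. That phrase is the aim of the separate sentence on optional testing, which could be carried out as a multigroup CFA. But that testing is conditional and names no model, so it does not close the gap. Nor does the article state a rule by which the scale would be declared invariant.
4. **Article-level detail.** The full sequence of invariance models may be left to a fuller document. However, the article does name a model and gives it a task it only partly performs.
5. **Legitimacy and harm.** A CFA with covariates is a recognised choice for intercept bias, many covariates or small subgroups. The Discussion makes clinical use and cutoffs depend on later research, so near-term clinical harm should not be claimed.

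**Conclusion.** The point holds in limited form. The only model named for invariance between subgroups assumes equal loadings, so on its own it supports at most a statement about intercepts. That conclusion rests on the model's structure alone.

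The size depends on assumptions. For one item at 0.70 v 0.35 with N = 500, detection by the direct-effect test ranges from about 4% (equal means, crossing at the mean), through 10-24% (0.3-0.5 SD mean difference, crossing near the mean), to nearly 100% (crossing 1 SD below the mean). In the last case the signal is labelled as intercept bias. In the settings crossing at or near the mean, the two-group loading test detects the difference in 99-100%. The loadings, the crossing point and the second-round N are not in the article. The change is cheap and worth making, but the defect does not invalidate the planned CFA.

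**What to change.** - For the main categorical characteristics already collected (sex, education, indication, and age split into groups), test equal loadings and then equal intercepts in a multigroup CFA on the second-round data.
- Where a subgroup is too small for separate models, add a factor-by-covariate interaction for each item. Keep the covariate model for continuous covariates.
- Run these tests whether or not the characteristic relates to the total score.
- Name the model intended for the optional testing by comorbidity level.
- If only the covariate model is run, report the result as no intercept bias detected, assuming equal loadings.

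**Cost.** The variables and the software (Mplus) are already in the plan, so the work is some extra model runs and a wording change. There will be more tests: four characteristics with 10-15 items give 40-60 item-level loading tests if each is examined singly, so an overall test per characteristic should come first. Power for small loading differences is modest in small subgroups. It was 80.5% for 0.70 v 0.50 even with two groups of 250. The second-round simulation could take this into account when N is set; if N is already fixed, small subgroups may have to be merged.

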### Sample Size

The sample size for phase 1 will be 8-12 experts. The sample size required for phase 2 to perform the Mokken scaling analysis was determined considering the 20 items derived from phase 1 (content validity phase). A simulation-based power analysis was performed in R (R Foundation for Statistical Computing; library “Mokken”), as shown in Multimedia Appendix 1. The aim of the simulation was to estimate a sample size that would provide sufficient statistical power, set at 0.8, to detect a minimum H coefficient of 0.3, indicative of a moderate scale according to Mokken’s hierarchy. The H coefficient in Mokken scaling analysis measures the strength of the hierarchical relationship among items in a scale as it quantifies the extent to which items form a cumulative scale. A custom simulation function was created using R statistical software, with the following parameters defined: 20 items, initial sample (n= 200), number of simulations=100, desired power=80%, minimum H coefficient=0.3, and maximum number of iterations=30. For each simulation iteration, the function generated a matrix of binary data representing responses to the 20 items, with responses simulated under a simple random model (ie, the probability of success was 0.5 for each item). The results from the simulation suggested that a sample size of 500 patients would be needed to achieve the desired power of 0.8 for our MSA. The MSA procedure will help reduce the number of items to the first 10-15 items that define the preparedness for self-monitoring and self-management of oral anticoagulation in adult patients. The required sample size for the second round of data collection will be determined through Monte Carlo simulations, aiming to achieve a power of 0.8 for the confirmatory factor analysis (CFA) model.

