In phase 2, validation procedures will be conducted to ensure the reliability and validity of the scale, and it is anticipated to end in September 2024. This process will require 2 cross-sectional data collections among Italian adult patients currently undergoing oral anticoagulation treatment. The collected data will be used to assess the scale’s psychometric properties and determine its performance in measuring preparedness for self-monitoring and self-management of oral anticoagulation [34]. More precisely, the first cross-sectional data collection will provide the needed power to perform the MSA procedure and determine item behavior in response to varying levels of the theoretical latent trait (preparedness) [35]. The second data collection will be based on the version of the scale updated from the analytics of the first data collection, and a CFA will be used to cross-validate the unidimensional structure of the PERSONAE scale. Cross-validation helps assess the generalizability of the scale’s results and allows researchers to determine if the validity holds true beyond the initial sample used for scale development [36].

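### The main measurement-invariance analysis runs only after a total-score association, a weak screen for item bias, and any scale shortened in round 2 would have no independent confirmation

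*Protocol article*

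**What the plan says.** All the relevant statements on invariance are in the Data Analysis section of the protocol article, in the paragraph on the confirmatory factor analysis (CFA).

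- **Purpose of the CFA:** "CFA will be used to cross-validate the plausible unidimensional structure of the PERSONAE scale derived from the MSA, theoretically containing 10-15 items". It uses the second-round sample. Principal Findings adds: "The second data collection will be based on the version of the scale updated from the analytics of the first data collection".
- **Entry condition:** "A confirmatory factor analysis with covariates will be used to estimate measurement invariance between subgroups if linear relationships between participant characteristics" and the total score are found.
- **Search for offending items:** "Modification indices will be explored to identify items causing a violation of invariance".
- **Action on them:** "Items causing invariance will be evaluated for possible deletion from the final scale".
- **A second route:** "Invariance testing based on different levels of CCI and other potential confounders will be considered if needed and is feasible". The stated aim of this route is equivalent functioning across levels of comorbidity and demographics.

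No sample after the second round is described.

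**The concern.** Measurement invariance asks whether an item behaves the same way in two groups of patients who are equally prepared. An association between a characteristic and the total score does not answer that. Groups may differ in total score because they differ in preparedness, with every item sound. They may also have equal totals although items are biased: biases of opposite sign cancel, one biased item is diluted in a total of 10-15 items, and an item that discriminates differently between groups may leave the mean unchanged. The condition can therefore stop the analysis in settings where bias is present but hidden.

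The second issue is the sample in which items may be removed. Round 2 exists to confirm a structure chosen in round 1. If items are dropped there after a search of modification indices, the resulting scale has been selected on the confirmation data, and its fit in those data is no longer a cross-validation.

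At stake is whether the study can claim equivalent functioning across patient groups, and whether the published item set is the one that was confirmed.

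**Working it through.** The plan gives no figure for the performance of this condition, so there is none to reproduce. The check asks how often the gate opens under different kinds of item bias.

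**Inputs from the protocol article.** Five-point items (rating scale); 10-15 items in the CFA; significance level 5% (Data Analysis), taken as two-sided.

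**Assumed inputs.** The round-2 sample size is not given ("The required sample size for the second round of data collection will be determined through Monte Carlo simulations"), so n = 200, 300 and 500 were used; the 500 in Sample Size is for the first-round Mokken analysis. Also assumed: one factor, loading λ = 0.7, two equal groups, and a bias of 0.5 SD of the latent item response.

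**Step 1: approximate arithmetic for the gate** (items treated as continuous, k = 12, n = 500).

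- Variance of the total = k + k(k − 1)λ² = 12 + 132 × 0.49 = 76.68, so SD = 8.757.
- Standardised group difference d = shift in total / SD. Noncentrality = d × √n / 2. Chance of opening = Φ(−1.96 + nc) + Φ(−1.96 − nc).
- One item biased: d = 0.5 / 8.757 = 0.057; nc = 0.057 × 11.18 = 0.64; chance about 10%.
- Two items biased by +0.5 and −0.5: shift 0, so the chance is 5%.
- Three items biased the same way: d = 1.5 / 8.757 = 0.171; nc = 1.92; chance about 48%.
- No bias, true trait difference of 0.3 SD: shift = 12 × 0.7 × 0.3 = 2.52; d = 0.288; nc = 3.22; chance about 90%.

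**Step 2: simulation with five-category items.** 1,000 replicates per cell, n = 200 to 500, k = 10, 12 and 15. The gate is a Pearson test of group against total score at 5%. The direct test regresses item 1 on rest score, then adds group and group × rest score (2 df, 5%).

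| Scenario | Gate opens | Direct test of item 1 rejects |
|---|---|---|
| No bias, no difference | 4-6% | 3-4% |
| One item +0.5 SD | 5-10% | 98-100% |
| Two items, +0.5 and −0.5 SD | 4-6% | 99-100% |
| One item, loading 0.7 in one group and 0.3 in the other | 5-6% | 79-100% |
| Three items +0.5 SD | 18-58% | 88-100% |
| No bias, true difference 0.3 SD | 50-91% | 3-6% |

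At k = 12 and n = 500 the simulated gate rates for one item, three items and a true difference are 9%, 46% and 91%, in line with Step 1.

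**Step 3: a separate simulation** with loading 0.65, 12 items, n = 500 and 600 replicates, testing every item with a Bonferroni correction over 12. One item biased by 0.5 SD: gate 9%, direct test 100%. Opposite biases: gate 3%, direct test 100%. Three items biased by 0.4 SD and offset by a true mean difference: gate 6%, direct test 100%. No bias and no difference: gate 6%, direct test 4.5%. High detection in Step 2 is therefore not an artefact of knowing which item to test.

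**Step 4: deletion.** Set side by side, the Data Analysis text makes the CFA the cross-validation and allows items to leave the final scale after a modification-index search within that CFA. With no later sample described, a shortened version is both chosen and assessed on the same data.

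**The case against.** Several defences of the plan stand and limit the point.

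- **The gate is not the only route.** A reader might infer that invariance is tested only after a total-score association. The text does not support this: testing by comorbidity index and other potential confounders is also foreseen. That route depends on need and feasibility, however, and names no criterion.
- **The gate is not unrelated to bias.** Bias in one direction across several items moves the total, as the 18-58% shows. The scenarios with low rates are those a total score is least able to see.
- **Opening the gate under a true difference does no harm.** That is a reasonable time to ask whether items behave equally, and the direct test then rejects in only 3-6%. The cost lies in bias that is missed.
- **Deletion is not automatic.** The text says only that items will be evaluated for it.
- **The rule is not reversed.** The phrase about items causing invariance might be read as a plan to remove sound items. The sentence before it speaks of a violation of invariance, so this is a slip of wording.
- **Rates for the whole study may differ.** The simulations screen one binary characteristic. The study procedures list nine. If each were screened independently at 5%, the chance of at least one false opening would be 1 − 0.95⁹ = 37%. The article does not say whether the model would then include all characteristics or only the one that triggered it. A claim that biased items would usually go undetected is therefore not established.
- **Reliability.** Nothing rules out recomputing it for a shortened scale, so its absence from the article is not itself a fault.
- **Use in practice is deferred.** The Discussion leaves cutoffs and clinical application to future research, which lowers the immediate stakes.

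None of this makes the total score a good screen, or supplies a confirmation sample for a scale shortened in round 2.

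**Conclusion.** The point holds in this limited form. The entry condition is a stated rule, so it is not detail left to a fuller document, and it is a weak and inconsistent screen for item bias. It opens in about 5-10% of samples for a single item biased by 0.5 SD and at about chance level for cancelling or non-uniform bias, but it does respond to several items biased the same way. The percentages rest on assumed loadings (0.65-0.7), bias sizes, equal groups and n = 200-500. The non-uniform result also depends on the two groups having the same mean trait level, centred where the item curves cross. The direction of the result does not depend on these values, because a total score cannot separate trait differences from item bias.

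Separately, if items are dropped in round 2, the final scale would have no independent confirmation within this protocol. This applies only if deletion occurs. The change is worth making before the round-2 analysis, since it decides what the study can say about equivalence across groups and about which item set was confirmed.

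**What to change.** 1. Remove the condition on a linear relation with the total score. Run the CFA with covariates for a fixed short list of characteristics already collected, for example age, sex, education, time on anticoagulation and indication, whatever their relation to the total.
2. Test direct effects of these characteristics on the items with a stated multiplicity correction.
3. Report the CFA before any deletion as the confirmatory result. Label any version after deletion exploratory, and recompute H and rho for it in the round-2 data.
4. Correct the slip so that the sentence refers to items causing non-invariance.

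The cost is a change of wording and a few more model runs, with no new data. The downside is a larger number of tests, which the correction handles.

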### Participants and Procedures

In phase 1, a panel of 8-12 experts, comprising nurses, physicians, and pharmacists, evaluated the relevance and clarity of the proposed items derived from the literature review (content validity). The experts provided written consent to use their sociodemographic and professional characteristics for scientific reporting, as content validity is closely linked to the characteristics of the involved experts. This phase cannot be anonymous to ensure transparency, and variables such as sex, age, academic title, experience in studies testing content validity, and experience in oral anticoagulation were collected.

Once adequate content validity was established (December 2023), data collection commenced at the IRCCS (Istituto di Ricovero e Cura a Carattere Scientifico [Institute for Research and Healthcare]) Policlinico San Donato, using 2 cross-sectional data collection rounds using web surveys. A convenience sampling procedure was used, disseminating the web surveys through social media campaigns, newsletters, and flyers of associations involving anticoagulated patients, such as “Associazione Italiana Cardiopatici Congeniti” (AICCA). Participants for the second round were selected based on the same approach, with communication to prevent overlapping responses from participants who completed the survey.

Quality control measures have been implemented to ensure the integrity and quality of the data collection process: automatic data validation checks are included in the survey software to ensure that all responses are complete and adhere to the required format; unique identifiers were used for each participant to prevent duplicate responses in the dataset; and after data collection, statistical analyses were performed to identify any outliers or inconsistencies in the responses, which were then reviewed for accuracy.

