### Data Analysis

The data analysis will involve the use of various statistical methods to develop and validate the PERSONAE scale.

For the first data collection round, MSA will be conducted using the “mokken” package in R [23]. MSA allows for the hierarchical evaluation of items, and the most relevant items that measure preparedness for self-monitoring and self-management of oral anticoagulation will be selected for the PERSONAE scale [24]. Loevinger’s coefficient of homogeneity function will be used to assess the scalability of the items. Monotonicity violations will be checked, and violations below 80 will be consistent with the requirements of a Mokken scale [23,25]. Loevinger’s coefficients of homogeneity (H) at the scale, item, and pairs of items level will be computed, where H values equal to or greater than 0.3, 0.4, or 0.5 indicate weak, moderate, or strong scales, respectively [23,25]. Item pairs violating monotonicity will be excluded, and floor and ceiling effects in data distribution will be assessed. Invariant item ordering (IIO) will be performed to further narrow down the pool of questions based on monotone homogeneity [25]. The IIO procedure will remove items one at a time until no significant violations are found. The Htrans (H^T^) coefficient will express the accuracy of the IIO selection, and H^T^>0.3 will denote proper IIO process and consistent Mokken scales. The final set of questions will be used to calculate ρ coefficients for reliability using the Molenaar-Sijtsma technique [26]. This approach is particularly adequate for assessing reliability in MSA because it provides a robust estimate of the internal consistency for nonparametric scales. The Molenaar-Sijtsma technique is well-suited for evaluating the scalability and reliability of the items within the scale, ensuring that the PERSONAE scale reliably measures the construct of preparedness for self-monitoring and self-management of oral anticoagulation.

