### Ethical Considerations

The present protocol was approved by the Ethical Committee of Ospedale San Raffaele (protocol number 52/INT/2023). Ethical considerations will be carefully adhered to throughout the research process.

In the first stage of the study, which involves experts assessing the content validity [29,30], written informed consent will be obtained from each expert. They will be fully informed about the study’s objectives and their voluntary participation in the process. During the second part of the study, data collection will be carried out through anonymous web surveys. As per European Regulation 2016/679 and Legislative Decree 101/2018, this type of study ensures anonymity and does not require individual written informed consent from the participants [31]. However, to ensure transparency and participant understanding, a simple and clear presentation page will be provided to patients before they proceed to complete the web-based questionnaire. This page will explain the study’s purpose, the voluntary nature of their participation, and the anonymity of the survey.

The research team will prioritize the confidentiality and privacy of all participants involved in the study, adhering to the ethical principles outlined in the Declaration of Helsinki. Personal data will be handled with utmost care, and all data collected will be stored securely and accessible only to authorized personnel involved in the study. Any potentially identifying information will be removed from the dataset to ensure complete anonymity. Throughout the study, participants’ rights and welfare will be protected, and any potential risks will be minimized. The study findings will be reported and disseminated in a manner that preserves anonymity and confidentiality. Researchers will act responsibly, maintaining the highest ethical standards and ensuring that the study is conducted with integrity and respect for the participants’ rights and well-being.

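### If an item is deleted after the round-2 factor analysis, the final PERSONAE scale will have been validated in no separate sample

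*Protocol article*

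**What the plan says.** **Purpose of round 2.** Study Design gives the second data collection the task of cross-validating the unidimensional structure found in the first. Principal Findings repeats this ("a CFA will be used to cross-validate the unidimensional structure of the PERSONAE scale") and adds that such cross-validation "allows researchers to determine if the validity holds true beyond the initial sample used for scale development".

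**What may happen to the items in round 2.** The CFA paragraph of Data Analysis provides for a CFA with covariates to examine measurement invariance, if participant characteristics are linearly related to the total score. Then: "Modification indices will be explored to identify items causing a violation of invariance". The next sentence is "Items causing invariance will be evaluated for possible deletion from the final scale". The paragraph gives no deletion criterion and no refit in new data, and does not say which item set the fit indices will be reported for.

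**Where scalability and reliability are estimated.** The Mokken paragraph of Data Analysis opens by naming the first round. It covers H, monotonicity, invariant item ordering with H^T, and finally reliability: "The final set of questions will be used to calculate ρ coefficients for reliability using the Molenaar-Sijtsma technique". For the CFA, the next paragraph lists only fit indices and invariance testing. The Abstract (Results) and Principal Findings make the same split: Mokken analysis in round 1, CFA in round 2.

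**The concern.** A cross-validation sample can test a scale only if the scale was fixed before the sample was examined. The CFA paragraph allows the item set to change after round-2 data have been searched. The version that leaves the study would then be partly a product of those data, with no further sample to test it in. The statement in Principal Findings about validity beyond the development sample would be true of the round-1 item set but not of the published one.

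The instruction is also worded backwards. One sentence looks for items that violate invariance; the next considers deleting items that cause it. Read literally, the second targets the well-behaved items.

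A smaller issue of the same kind arises in round 1. H and rho for the retained items are estimated in the sample in which those items were picked for scaling well, so they tend to be somewhat too high.

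**Working it through.** The plan states no figure on this point, so there is none of its own to reproduce. The one figure borrowed is the round-1 size of 500. It could not be recovered from the simulation model in Sample Size: independent binary items with success probability 0.5 gave a mean H of 0.000 and a maximum of 0.012 in 1000 runs at n = 500. The point here does not depend on it.

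**Step 1: the logic.**
- Items are selected in round 1, and structure is tested in round 2.
- If no item is deleted in round 2, the tested set equals the round-1 set. Selection and test then use different data collections, and the claim stands.
- If one or more items are deleted on round-2 modification indices, the final set depends on round-2 data. No later sample is planned, so the final set has no separate-sample test.

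**Step 2: could the second case arise by chance?** Inputs from the article: 10-15 items and a 5% significance level for all analyses. Assumptions: one test per item and covariate, independent tests, no multiplicity adjustment, no true non-invariance. The chance of at least one flagged item with m items and c covariates is 1 − 0.95^(m·c):
- 1 covariate: 1 − 0.95^10 = 0.401; 1 − 0.95^15 = 0.537.
- 3 covariates: 1 − 0.95^30 = 0.785; 1 − 0.95^45 = 0.901.

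The section on study procedures lists five sociodemographic and four clinical variables, nine in all, so several covariates are possible. These are chances of a flag, not of a deletion.

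**Step 3: how optimistic are the round-1 values?** Inputs from the article: 20 five-point items, 10-15 kept, n = 500 in round 1. Assumptions: a one-factor model, the loadings shown below, and a fresh sample also of 500 (the article leaves the round-2 size to Monte Carlo simulation). Items were removed one at a time by lowest item H. H is the sum of inter-item covariances divided by the sum of their maxima given the item distributions. Optimism is H in the selection sample minus H of the same items in fresh data, averaged over 400 runs per setting.

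| Assumed loadings | Items kept | H, selection | H, fresh | Optimism | Alpha, selection / fresh |
|---|---|---|---|---|---|
| all 0.6 | 10 | 0.382 | 0.353 | 0.0299 | 0.846 / 0.829 |
| all 0.6 | 15 | 0.366 | 0.353 | 0.0131 | 0.886 / 0.880 |
| 0.5-0.7 | 10 | 0.423 | 0.410 | 0.0125 | 0.866 / 0.860 |
| 0.5-0.7 | 15 | 0.389 | 0.379 | 0.0099 | 0.895 / 0.891 |
| 0.4-0.8 | 10 | 0.489 | 0.484 | 0.0053 | 0.893 / 0.891 |
| 0.4-0.8 | 15 | 0.418 | 0.414 | 0.0045 | 0.905 / 0.904 |

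H is inflated by about 0.005 to 0.030. Alpha, used as a stand-in for rho, is inflated by 0.001 (0.905 − 0.904) to 0.017 (0.846 − 0.829). The difference between the two samples has a standard deviation of 0.023 to 0.026 across runs, so the bias is at most about the size of ordinary sampling noise (0.030 / 0.025 = 1.2).

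It can still change a classification close to the cut-off. A separate simulation of 400 sample pairs at n = 500, with equally good items and the 10 highest item H values kept, gave H = 0.322 in the selection sample and 0.292 in fresh data, on either side of 0.30. The alpha gap there was 0.807 − 0.784 = 0.023. With unequal items the same exercise gave 0.366 against 0.359.

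**The case against.** **Deletion is doubly conditional.** Invariance is examined only if a covariate is related to the total score, and deletion is then only possible. This stands. A reader might infer that round 2 is not an independent validation at all; the article does not support that, because with no deletion it is one. The trigger is nevertheless weak: a covariate can be related to the score because preparedness truly differs between patients, without any faulty item.

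**The round-2 step targets non-invariance, not poor fit or low H.** This also stands. The deletion step itself was not simulated, so no amount of optimism in round-2 fit can be claimed. The objection to that step is the loss of a separate-sample test.

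**The round-1 optimism is small, and nothing says H or rho is computed in round 1 only.** Both are fair. The 0.30 crossing needs equally good items, a fresh-data H just under the threshold and the largest cut. That the coefficients belong to round 1 is read from the layout of three sections, which agree, but a fuller plan could add them to round 2. The article claims cross-validation of the structure, not of H or rho, so reporting them again is an improvement and removes no contradiction.

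**Repeat responders.** Both rounds recruit in the same way and "data collection will be carried out through anonymous web surveys", so a reader might infer that people who answered twice cannot be detected. The article does not support this. Participants and Procedures states that "unique identifiers were used for each participant to prevent duplicate responses in the dataset" and that round-2 recruitment was done "with communication to prevent overlapping responses from participants who completed the survey". A non-identifying code is compatible with anonymity. How identifiers link the rounds is not described, but that is detail an article may leave out and is no part of this point.

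**Conclusion.** The point holds in conditional form. The CFA paragraph permits a change to the item set on the data that Study Design and Principal Findings reserve for testing it. Any scale shortened that way would lack the separate-sample validation the article claims; a scale left unchanged would have it. A chance flag is a realistic prospect: 40% to 54% for one covariate and 79% to 90% for three, if tests are independent, unadjusted and there is no true non-invariance.

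The round-1 optimism is secondary: about +0.005 to +0.030 for H and 0.001 to 0.023 for alpha across the n = 500 settings above. These sizes rest on assumed loadings and thresholds, on selection by item H alone (the monotonicity and item-ordering removals were not modelled), and on alpha in place of rho. H^T was not simulated. The effect matters mainly if the scale lands near 0.30. The reversed wording about invariance is a plain error.

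**What to change.** Amend the CFA paragraph of Data Analysis to say:

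1. The item set is frozen after the round-1 Mokken analysis.
2. The fit of that unmodified one-factor model in round 2 is the primary validation result and is reported whatever the invariance analyses show.
3. H, H^T and the Molenaar-Sijtsma rho are also reported for the frozen set in round 2, beside the round-1 values.
4. Invariance analyses proceed as planned, but any version shortened because of them is labelled provisional and not cross-validated until tested in new data.
5. The deletion sentence refers to items violating invariance.

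The cost is a few sentences and one extra R run on data already being collected. The reported reliability and scalability may come out slightly lower. All five changes can still be made if round-2 data collection has closed.
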